**Figure 3 figure3:**

Process of online-mediated EZI-PrEP care. It should be noted that 6 months after inclusion, the video consultations will become optional, and PrEP provision will then be based on online (self-reported) medical history and test results. A currency exchange rate of €1=US $1.05 is applicable. EZI-PrEP: E-Health for Zero Infections - facilitating access to and use of Pre-Exposure Prophylaxis in the Netherlands; PHS: public health service; PrEP: pre-exposure prophylaxis.

### EZI-PrEP Applications

#### EZI-PrEP App

All participants will get access to the free-of-charge, password-protected EZI-PrEP app through the Apple and Google Play stores. App functionalities will depend on their allocated mode of PrEP care provision. All participants will have access to the daily diary, the summary of data entered in the diary, and a timeline with an overview of upcoming PrEP monitoring visits and study questionnaires (Figure 4). Participants receiving online PrEP care will also receive access to the online-mediated test request platform, video consultation software, and PrEP payment module. All functionalities will be immediately accessible by clicking on the activity in the timeline of the app via a single sign on. All participants will be able to receive messages in the app from SHC health care workers and study staff, but will not be able to send messages via the app (Figure 4).

**Figure 4 figure4:**
[figure not shown]
Homepage of the EZI-PrEP app. It should be noted that Testlab package 2 and online PrEP consultation are only visible to EZI-PrEP participants in arms 3 and 4. Arm 3: online monitoring every 3 months; Arm 4: online monitoring every 6 months; EZI-PrEP: E-Health for Zero Infections - facilitating access to and use of Pre-Exposure Prophylaxis in the Netherlands; PrEP: pre-exposure prophylaxis.

#### EZI-PrEP Administration Portal

The EZI-PrEP app and all functionalities, except for the diary, will be controlled by SHC health care workers and EZI-PrEP study staff via a web portal that uses a cloud platform to exchange data with the EZI-PrEP app. The administration portal will be used to activate participant accounts, with functionalities enabled according to the study arm allocation. The portal will include an event planner to register the date and time of in-clinic visits, online-mediated testing, and video consultations, and activate the PrEP payment module upon entering the number of tablets that can be obtained by the online participants. The portal will also be used for scheduling questionnaires and, for online participants only, to activate home delivery of a DBS home sampling kit. In-app messages will be sent via the administration portal as well. Health care workers will be able to only access the accounts of participants receiving PrEP care at their SHCs.

### Laboratory Procedures

Laboratory procedures will be performed according to routine STI and PrEP care clinical protocols, which may slightly differ across study sites. A detailed description of the laboratory procedures at each study site can be found in Multimedia Appendix 1.

### Data Collection Methods

#### EZI-PrEP Diary

To minimize recall bias and increase the accuracy of self-reported PrEP intake, casual anal sex, and condom use, participants will be requested to complete a daily diary for primary outcome measurement [50]. Completing the diary may be burdensome for certain participants and could result in less motivation to remain in the study. Minimizing the length of the diary collection period could help maintain sufficient motivation to complete the diary and continue study participation. During the first 18 months of the study, each participant will be completing 4 to 6 daily questions. These diary questions ask about PrEP use, sexual behavior of the previous day, and current mood. The first question (“Do you use daily or event-driven PrEP?”) will be asked once and set as default (ie, prefilled) until the participant changes to a different regimen, which can be selected in a new diary on the following day. The second question (“How many PrEP pills did you take?”) will need to be answered with 0, 1, or 2. In case of 1 or 2 tablets, the third question will be prompted (“At what time did you take PrEP?”), which will need to be answered with a specific time. The fourth question (“Did you have anal sex with a casual partner?”) will need to be answered with yes or no. If yes is answered, the fifth question (“Did you use a condom every time?”) will be prompted, which will need to be answered with yes or no. The sixth question (“How do you feel today?”) will need to be answered on a discrete scale with 5 options, ranging from 1 (depicted by a red sad face) to 5 (a green happy face). Participants will be allowed to change their answers until automatic submission of the diary when the final question is answered. The average expected duration of completing the daily diary is 90 seconds.

The diary that is completed on a given day will ask about PrEP intake and sexual behavior of the day before, which is indicated on the top of the screen. If a participant forgets to enter their information in the daily diary, they will be allowed to retrospectively fill in information, but only for the past 2 days.

To increase diary completion adherence, we will send automated daily notifications at 10 AM Central European Time (CET); however, it will be possible to deactivate this reminder in the settings of the app. If a participant has not completed their diary for 7 days, an email with a reminder and explanation of the importance of the diary for the study will be sent. After 14 days, another reminder that the diary is crucial for the study will be sent to the participant and to the PHS where they are under care, so that the importance of diary completion can be discussed in the upcoming monitoring visit. Being unable to complete the diary will not be considered as a reason to end participation in the study.

#### DBS Collection

We will collect DBSs to measure intracellular concentrations of TFV-DP and emtricitabine-triphosphate (FTC-TP). Blood will be spotted on Whatman 903TM Protein Saver Cards (GE Healthcare Bio-Sciences Corp). For participants receiving in-clinic PrEP care, study nurses will collect whole blood via phlebotomy and spot this onto the DBS card during the 6- and 12-month PrEP monitoring visits. Participants receiving online-mediated PrEP care will receive a DBS home sampling kit after completing their PrEP monitoring visit at months 6 and 12. This kit contains the DBS card with 5 spots, 2 contact-activated lancets (2.0-mm BD Microtainer), an alcohol wipe, a gauze wipe, 2 band aids, a grip seal bag, a desiccant sachet with a humidity indicator (MiniPax, Multisorp Technologies), a preposted envelope, and paper instructions with a QR code to an instruction video. Participants will be requested to send the completed DBSs in the preposted envelope to the Amsterdam regional microbiology laboratory. All DBS cards will be stored at −20°C at the Amsterdam regional microbiology laboratory and shipped in batches for analysis to Skaggs School of Pharmacy and Pharmaceutical Sciences (University of Colorado Anschutz Medical Campus). Owing to financial constraints, only DBS cards from daily PrEP users will be analyzed. The procedure to measure TFV-DP and FTC-TP in DBSs has been described previously [51]. The results will not be reported back to the participants. For participants with incident HIV infection, the most recent DBS prior to infection will be analyzed for TFV-DP, FTC-TP, and HIV RNA

#### Clinical Data

We will obtain the clinical data of all PrEP and STI consultations of study participants between enrollment and study completion from the Dutch national SHC surveillance database (SOAP). During every consultation at the SHC, data are collected on the following: (1) sociodemographic characteristics (age, gender, highest educational level, country of birth, and country of birth of parents); (2) sexual behavior and STI/HIV risk factors (number of sex partners, condom use, group sex, use of alcohol and drugs during sex, sex work, having been a victim of sexual violence, and sex partners from STI or HIV endemic countries); (3) reason for consultation (partner notification, STI-related symptoms, PrEP, and STI testing); (4) PrEP use (history of PrEP use, reasons for stopping PrEP, and number of PrEP tablets provided); and (5) HIV infection, STI, and HCV infection testing and diagnosis. Data on kidney function and proteinuria will be retrieved from the electronic patient files.

#### Study Questionnaires

The first 4 questionnaires (ie, at baseline, and 6, 12, and 18 months) will ask about PrEP intake, sexual behavior, risk perception related to STIs and HIV infection, and STI testing at facilities other than SHCs. We will include several psychosocial measurements in the questionnaires (summarized in Table 2). The questionnaire at month 12 will include questions on social norms with respect to PrEP use, loneliness, and the presence of social support systems. To investigate the usability and acceptability of the PrEP care modality, we will include questions based on Davis’ model of technology acceptance [52] at months 6, 12, and 18. These questionnaires will also include questions regarding experiences with PrEP care and to what extent participants felt supported in their PrEP use. To assess the usability and acceptability of online-mediated PrEP care specifically, we will include the system usability scale [53] at month 18 for online study participants. We will also ask them to rate the different steps during their online PrEP care. The fifth (and last) questionnaire, at month 24, will focus on the quality of PrEP care within the EZI-PrEP study and in the Netherlands in general, as well as the time and cost investments of study participants in receiving PrEP care.

**Table 2 table2:** Overview of psychosocial measurements within the EZI-PrEP study in each survey round.

Scale	Abbreviation	Aspect measured	Baseline survey (month 0)	Follow-up survey			
				Month 6	Month 12	Month 18	Month 24
Self-reported habit index	SHI	Habit formation	✓	✓	✓	✓	
Patient Health Questionnaire-9	PHQ-9	Severity of depressive symptoms	✓	✓	✓	✓	
Generalized Anxiety Disorder Assessment	GAD-7	Generalized anxiety disorder	✓	✓	✓	✓	
Sexual compulsivity scale	SCS	Sexual compulsivity	✓		✓		
Alcohol Use Disorders Identification Test	AUDIT	Problematic alcohol use	✓			✓	
Drug Use Disorders Identification Test	DUDIT	Problematic drug use	✓			✓	
Perceived stress questionnaire	PSQ20	Perceived stress		✓	✓	✓	
Brief Resilience Scale	BRS	Resilience		✓			
Cognitive Emotion Regulation Questionnaire	CERQ-short	Coping skills			✓		
HEXACO^a^ Personality Inventory-Revised	HEXACO-PI-R	Conscientiousness			✓		

^a^HEXACO is an acronym for “Honesty-humility,” “Emotionality,” “Extraversion,” “Agreeableness,” “Conscientiousness,” and “Openness to experience.”

### Data Analysis

#### Primary Outcome

The primary outcome (“unprotected act”) will be assessed using daily self-reported data on sexual behavior, pill intake, and condom use. We will use all available data, meaning that observation time and all data of those who are lost to follow-up or have dropped out will be included until their last day in the study. We will determine, for each day of follow-up, whether a condomless anal sex act with a casual partner took place. We will also determine whether sufficient PrEP pills were taken around the time of this condomless anal sex act. Using this information, the condomless anal sex act will be considered as either unprotected or not. We will then calculate the total number of unprotected acts (n) and the total person-years of observation. Incidence rates per 100 person years will be calculated by dividing the sum of all unprotected acts by the sum of person-years of observation and multiplying the result by 100. We will calculate the incidence rates among participants of online PrEP care (arms 3 and 4), in-clinic PrEP care (arms 1 and 2), monitoring every 6 months (arms 2 and 4), and monitoring every 3 months (arms 1 and 3). Two main analyses will be conducted in which we will test the ratio of the incidence rates of unprotected acts for (1) online PrEP care versus in-clinic PrEP care and (2) monitoring every 6 months versus monitoring every 3 months. The analyses will be based on crude unadjusted incidence rate ratios.

A noninferiority trial intends to demonstrate that one intervention is not unacceptably worse than a comparison intervention [54]. To do so, the lower limit of the 95% CI (or 2-sided 97.5% CI) should not extend beyond a predefined margin, which is referred to as the noninferiority margin. In this study, noninferiority will be tested using a 1-sided test based on maximum likelihood estimators with a type 1 error at 0.0125 (ie, with 2 comparisons using Bonferroni corrections=0.025/2) [40] and a noninferiority ratio of 1.8. If the upper 2-sided 97.5% CI of the incidence rate ratio is below 1.8, we will conclude that the intervention arms are noninferior to the comparator arms.

To determine whether the incidence rates change over time, we will model the number of unprotected acts as a function of 1-month intervals using Poisson regression (or negative-binomial regression, if the standard deviation is far greater than the mean of the outcome, ie, overdispersion) and test for changes in time using a Wald χ^2^ test. We will test for the interaction between time and intervention arm.

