### Randomization

Participants will be randomized (stratified by PHS and by PrEP experience, that is, those starting or restarting PrEP, and current PrEP users) to 1 of 4 study arms in permuted blocks of 4. Randomization will be performed by a statistician of PHS Amsterdam who is not part of the EZI-PrEP study team at initiation of the study, using Stata Intercooled 15.1 (StataCorp). Sequentially numbered and colored nontransparent envelopes will be made, containing a code for the study arm. Each PHS will receive 2 sets of envelopes, red ones for those starting or restarting PrEP and blue ones for current PrEP users. During the enrollment interview, in the presence of the participant and dependent on their PrEP experience, the health care provider will open the next envelope to reveal the study arm and study number.

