### Power and Sample Size Calculation

We assume that the primary outcome measure of unprotected acts will be Poisson distributed with the total number per 100 person-years given as an incident rate (λ) and the total time during monitoring (*t*). We define the incidence rate in the experimental arm as λ_e_ and the incidence rate in the control arm as λ_c_. We aim to reject the null hypothesis that the ratio λ_e_/λ_c_ is greater than or equal to a predetermined noninferiority ratio (r). We consider that a noninferiority ratio of 1.8 is able to preserve clinically acceptable noninferiority bounds with increasing λ.

In a previous PrEP study in the Netherlands (Amsterdam PrEP demonstration project [“AMPrEP study”]), the overall incidence rate of unprotected acts was 78/100 person-years [50]. The AMPrEP study included participants with a high number of sex partners and very high incidence of bacterial STIs. Participants of the NPP have reported fewer casual sex partners and have a lower incidence of bacterial STIs [55]. The EZI-PrEP participants are therefore expected to have fewer unprotected sex acts than the AMPrEP participants. We expect the incidence rate of unprotected acts in the experimental arm (λ_e_) and control arm (λ_c_) to be at least 36/100 person-years. We also assume a median monitoring time of 18 months. Using a Bonferroni-corrected 1-sided type 1 error of 0.0125 (=0.025/2 for a total of 2 comparisons), we will need 368 participants to have 90% power to demonstrate noninferiority using the test statistic based on maximum likelihood estimators from Stucke and Kieser [56]. If λ is higher than 36/100 person-years, we will have sufficient power to demonstrate noninferiority. Considering expected loss to follow-up, we have increased the target sample size by 20%, and thus, the total required sample size is 442.

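### Both primary rate ratios are fixed as crude, leaving out the randomisation strata and pre-randomisation sexual behaviour: a loss of precision, not a bias

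*Protocol article*

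**What the plan says.** Under Primary Outcome, the protocol article pools unprotected acts and person-years over the arms on each side of each comparison (online against in-clinic, 6-monthly against 3-monthly). It then states: "The analyses will be based on crude unadjusted incidence rate ratios". Noninferiority is claimed if the upper limit of the 97.5% interval lies below 1.8. The regression models described afterwards serve the time trend and the analysis of determinants, not these two comparisons.

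Under Randomization, allocation is "stratified by PHS and by PrEP experience, that is, those starting or restarting PrEP, and current PrEP users", which with four PHS gives eight strata.

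Sexual behaviour is collected in two places:
- Clinical Data lists, for every consultation, "sexual behavior and STI/HIV risk factors (number of sex partners, condom use, group sex" and further items.
- Study Questionnaires says: "The first 4 questionnaires (ie, at baseline, and 6, 12, and 18 months) will ask about PrEP intake, sexual behavior".

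Enrollment Procedures puts the regular PrEP consultation first, then consent, then randomisation, then onboarding to the app.

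Under Power and Sample Size Calculation, the planning model has no dispersion term: "We assume that the primary outcome measure of unprotected acts will be Poisson distributed". The same section reasons from fewer casual partners and fewer bacterial infections to a lower outcome rate: "The EZI-PrEP participants are therefore expected to have fewer unprotected sex acts than the AMPrEP participants".

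**The concern.** Noninferiority turns on one upper confidence limit, so avoidable variance can cost the conclusion. The planning rate implies about half an act per person over 18 months, so a small number of very active participants can dominate a pooled rate. Stratifying by site and PrEP experience does not balance such persons between arms. The trial records behaviour before allocation that the protocol itself links to the outcome rate, yet the crude ratio leaves it in the error term. With a log link, adjustment leaves the target rate ratio, and so the 1.8 margin, essentially unchanged. The precision would therefore come at no cost in interpretation.

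**Working it through.** **Inputs from the protocol article (power section).** Rate 0.36 per person-year in both arms, 1.5 years, margin 1.8, one-sided alpha 0.0125, 90% power, 368 evaluable participants, hence 184 per side of each comparison. Mean acts per person: mu = 0.36 × 1.5 = 0.54.

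**Assumptions, not in the documents.** kappa is the squared coefficient of variation of persons' underlying rates. R is the share of kappa explained by baseline covariates.

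**The plan's own figure.** With kappa = 0, the usual formulas at the stated inputs give 268 (log-ratio Wald), 276 (restricted maximum likelihood) or 306 (unrestricted), not 368. At 368 they give 95 to 97% power. The step 368 × 1.2 = 442 reproduces. This discrepancy is a separate matter. Here 368 is used only as the planned evaluable number.

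**Formulas.** Variance term per person on the log-rate scale: V = 1/mu + kappa(1 − R), with R = 0 for the crude analysis. SE = √(2V/184). Power = Φ(ln 1.8/SE − 2.2414), with ln 1.8 = 0.5878.

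Example, kappa = 2:
- Crude: V = 1.852 + 2 = 3.852, SE = 0.205, power = Φ(0.5878/0.2046 − 2.2414) = 74%.
- Adjusted, R = 25%: V = 1.852 + 1.5 = 3.352, SE = 0.191, power 80%.

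| kappa | Power, crude | R = 10% | R = 25% | R = 50% | Variance removed (R = 10 / 25 / 50%) |
|---|---|---|---|---|---|
| 0 | 97% | 97% | 97% | 97% | 0 / 0 / 0% |
| 1 | 86% | 88% | 90% | 92% | 4 / 9 / 18% |
| 2 | 74% | 76% | 80% | 86% | 5 / 13 / 26% |
| 4 | 54% | 57% | 63% | 74% | 7 / 17 / 34% |

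For 90% power at kappa = 2 and R = 25%, about 554 participants are needed crude and 482 adjusted.

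**Strata alone.** Take 25% starters or restarters (the intended minimum under Study Population) and assume they have twice the rate of current users. The squared coefficient of variation due to this factor is 0.25 × 0.75/1.25² = 0.12. As a share of V at kappa = 2 it is 0.12/3.85 = 3%. Any site effect comes on top, and the documents give no figure for it.

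**Check by simulation** (Poisson regressions, 1,500 runs per scenario, R = 25%). The standard deviation of the log rate ratio, crude and adjusted, was 0.175 and 0.166 (kappa 1), 0.206 and 0.193 (kappa 2), and 0.248 and 0.227 (kappa 4). Power with robust standard errors went from 87 to 90%, 74 to 81% and 61 to 69%. At kappa = 4 these powers exceed the formula's, partly because the robust standard error ran somewhat small (0.237 against 0.248 crude). The model-based Poisson standard error stayed at 0.143 to 0.144, with or without the covariate.

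**The case against.** **The gain rests on undocumented inputs.** This stands. Neither kappa nor R is in the documents, and under the protocol's own Poisson assumption the gain is nil. R may be modest: the outcome is condomless casual sex that PrEP did not cover, so adherent participants with much condomless sex add few events. The protocol's link between partner numbers and the outcome compares cohorts, not individuals. Hence a range is given, not one figure.

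**Most of the lost power comes from overdispersion, not from lack of adjustment.** This stands too. A reader might infer that the planned interval is too wide because the strata are ignored. That would be true only of an analysis whose variance already allows for overdispersion. The protocol describes a maximum-likelihood test on an outcome assumed to be Poisson. With overdispersion, that test's standard error would be too small, which is a different and larger problem.

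**The crude ratio is valid and matches the sample-size test.** Agreed. A reader might infer bias from the lack of adjustment, but randomisation rules that out in expectation.

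**Leaving out the other factorial factor is no loss.** Agreed. With four arms in permuted blocks of 4, each factor is balanced over the other, and no loss of precision can be shown.

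**The baseline questionnaire may not be a baseline measure.** This stands. Nothing says that it is completed before allocation, and the trial is open-label. Only the intake consultation is placed before randomisation.

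**An adjusted model may weight persons differently.** Partly stands. A negative binomial model does not weight by person-time as the pooled ratio does, so with unequal diary time the estimate could move. A Poisson log-link model with robust variance stays closer to the pooled ratio.

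**Adjustment can be left to the analysis plan.** Not here: the protocol article fixes the primary analysis as unadjusted.

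**Conclusion.** The point holds as one of efficiency. Both primary comparisons are fixed as crude, and covariates available before randomisation are left out. If they explain 25% of the between-person variation, the gain at 368 participants is about 4, 6 and 9 percentage points of power for kappa of 1, 2 and 4. It is nil without heterogeneity. These figures assume a true ratio of 1, 18 months of follow-up for everyone and a dispersion-aware variance. The share due to the strata is probably small, so behaviour at intake would carry most of any gain. The change is worth making because it needs no new data. It is not a flaw that invalidates the trial.

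**What to change.** Replace the sentence that fixes crude ratios with one prespecified primary model:

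- A log-link rate model with a person-time offset and a robust (or negative binomial) variance. The variance is essential, since adjustment alone would leave the reported interval almost unchanged.
- Terms for both randomised factors (so that one model yields both ratios), PHS, PrEP experience and one prespecified measure of sexual behaviour from the intake consultation. Use the baseline questionnaire only for participants shown to have completed it before allocation, or not at all.
- A stated rule for missing covariate values.
- Both rate ratios and their 97.5% intervals taken from this model and judged against 1.8, with the crude ratio reported as a sensitivity analysis.

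The cost is wording in the protocol and analysis plan, settled before outcome data are compared by arm. It also needs a check that the enrolment-visit record is part of the surveillance extract. No new data collection is needed.

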**Objective:**

The primary objective of this study is to establish the noninferiority of online PrEP care (vs in-clinic care) and monitoring every 6 months (vs every 3 months). The secondary objectives are to (1) examine differences between PrEP care modalities regarding incidences of STIs, HIV infection, and hepatitis C virus infection; retention in PrEP care; intracellular tenofovir-diphosphate concentration; and satisfaction, usability, and acceptability of PrEP care modalities; and (2) evaluate associations of these study outcomes with sociodemographic, behavioral, and psychological characteristics.

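### Plain Bonferroni on the two primary noninferiority tests is valid, but Holm's step-down gives more power for the same one-sided familywise error of 0.025

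*Protocol article*

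**What the plan says.** The Abstract sets out to "establish the noninferiority of online PrEP care (vs in-clinic care) and monitoring every 6 months (vs every 3 months"; that is two claims, and both are wanted. Data Analysis, Primary Outcome confirms this: "Two main analyses will be conducted in which we will test the ratio of the incidence rates of unprotected acts". The same section fixes the one-sided error of each test at 0.0125 ("with 2 comparisons using Bonferroni corrections=0.025/2") with "a noninferiority ratio of 1.8". It decides each comparison separately by its own interval: "If the upper 2-sided 97.5% CI of the incidence rate ratio is below 1.8", noninferiority is concluded. The Methods paragraph of the Abstract gives the same rule.

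Power and Sample Size Calculation uses the same level ("Bonferroni-corrected 1-sided type 1 error of 0.0125 (=0.025/2 for a total of 2 comparisons") and states that "we will need 368 participants to have 90% power to demonstrate noninferiority". The target is then raised by 20%, to 442. No step-down, ordering or passing-on of error between the two tests is described.

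**The concern.** Once one comparison has succeeded at 0.0125, only one null hypothesis is left that could be rejected wrongly. Testing it at the full one-sided 0.025 keeps the familywise error at or below 0.025. Plain Bonferroni still holds it to 0.0125, so half of the permitted error goes unused in exactly that situation.

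The case at stake is a second comparison with a one-sided p-value between 0.0125 and 0.025, after the first has been shown noninferior. Under the stated rule that claim is lost; under Holm it is made. This matters because online care and 6-month monitoring are separate policy questions and the trial wants an answer to both.

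**Working it through.** **Inputs from the protocol article.** One-sided error 0.0125 per test; margin r = 1.8; rate λ = 0.36 per person-year in both arms; follow-up t = 1.5 years; Poisson counts; 90% power; 368 evaluable participants. Four arms in permuted blocks of 4 are taken as equal allocation, so each factor compares 184 with 184.

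**Step 1. Reproduce 368.** With the unrestricted maximum-likelihood variance, the number per factor level is

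n = (z(1−α) + z(power))² × U, with U = λ(1 + r²) / t / ((r − 1)λ)²

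U = 0.36 × 4.24 / 1.5 / 0.288² = 1.0176 / 0.082944 = 12.27.

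- 90% as power for both claims, near-independent contrasts: each test needs √0.90 = 0.9487. Then n = (2.241 + 1.632)² × 12.27 = 184.09, total 368.2. This matches 368, and 368 × 1.2 = 441.6 gives 442.
- 90% as power for one test: n = (2.241 + 1.282)² × 12.27 = 152.3, total 306 after rounding up each level. The restricted maximum-likelihood version gives 275 and the log rate ratio version 266. None matches.

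The article does not say which reading is meant; the joint one is inferred from this match.

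**Step 2. Power of each test at 368.** Standardised shift s = √(184 / 12.27) = 3.873.

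- At 0.0125: p1 = Φ(3.873 − 2.241) = 0.9486.
- At 0.025: p2 = Φ(3.873 − 1.960) = 0.9721.

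**Step 3. Bonferroni against Holm.** Holm makes both claims when both p-values are at most 0.025 and at least one is at most 0.0125. For independent contrasts:

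- Both claims, Bonferroni: p1² = 0.900.
- Both claims, Holm: p2² − (p2 − p1)² = 0.9450 − 0.0006 = 0.944.
- Each claim, Bonferroni: p1 = 0.949.
- Each claim, Holm: p1 + (p2 − p1)p1 = 0.9486 + 0.0235 × 0.9486 = 0.971.
- At least one claim, either procedure: 1 − (1 − p1)² = 0.997.

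With all 442 followed and no loss, power for both is 95.5% against 97.8%.

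**Step 4. If power is lower than planned (assumed values).**

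| Power per test at 0.0125 | Shift | Power at 0.025 | Both, Bonferroni | Both, Holm |
|---|---|---|---|---|
| 90% | 1.282 + 2.241 = 3.523 | 94.1% | 0.90² = 81% | 0.941² − 0.041² = 88% |
| 80% | 0.842 + 2.241 = 3.083 | 86.9% | 0.80² = 64% | 0.869² − 0.069² = 75% |

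From the planned shift of 3.873, these rows correspond to variance inflation of (3.873 / 3.523)² = 1.21 and (3.873 / 3.083)² = 1.58, if the analysis allows for it. The article gives no dispersion value. It does foresee overdispersion in its model for change over time, and its Discussion expects missing diary data. In the first row, a correlation of −0.3 to 0.3 between the contrasts moves the Holm figure only between 88.2% and 88.9%.

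**Step 5. Familywise error.** In simulation with both nulls true it was 0.0248 under either procedure, agreeing with 1 − (1 − 0.0125)² = 0.0248. With one null true and the other certain to be rejected, it was 0.0125 under Bonferroni and 0.0250 under Holm. A Poisson simulation of the 2×2 design with 92 per arm gave 0.0215 for both procedures in the first case, and 0.0105 and 0.0220 in the second. Its power for both claims was 92.3% against 95.9%.

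**The case against.** The plan is consistent and valid. The Abstract, the Primary Outcome section and the sample size section agree on the error rate, the interval and the margin, and 368 was calculated at 0.0125, so the cost of Bonferroni is already paid in participants. All of this stands, and it makes the point an improvement in efficiency.

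Two further arguments have weight. First, the rule decides by confidence interval. Under Holm a second claim can be declared although its 97.5% interval crosses 1.8, and this occurs exactly where Holm changes the result. Bonferroni keeps decision and interval aligned. Second, if one modality is truly inferior and the other succeeds, the chance of wrongly passing the inferior one is up to 0.025 under Holm instead of 0.0125. With an outcome that stands in for HIV risk, holding each modality to 0.0125 can be defended. Even so, the 0.025 lies within the familywise limit that the protocol chose, and the mismatch can be handled by also reporting the 95% interval that decides the second claim.

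A reader might infer that the plan gives only 81% power for both claims. The article does not support this: it never calls the 90% a per-test figure, and 368 is reproduced under the joint reading. A reader might also infer that the target could be cut, since Holm needs about 318 evaluable participants for 90% power on both. That holds only if the Poisson and follow-up assumptions hold, and the article itself doubts them.

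**Conclusion.** The point holds as a low-cost improvement to a stated method. The planned analysis is neither invalid nor, on its own assumptions, underpowered. The gain at 368 is 4.4 points in power for both claims (94.4 − 90.0) and 2.2 points for each claim (97.1 − 94.9), with nothing added to the chance of at least one claim. These figures rest on equal true rates of 0.36 per person-year, Poisson counts, 18 months of follow-up, equal allocation and near-independent contrasts. The larger gains, about 7 points at 90% per test and 11 points at 80%, apply only if power falls short of plan. Holm's control of the familywise error needs none of these assumptions.

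**What to change.** In the Abstract (Methods) and in Data Analysis, Primary Outcome, replace the decision rule with wording such as:

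*The two one-sided p-values will be ordered. Noninferiority will be concluded for the comparison with the smaller p-value if the upper limit of its 2-sided 97.5% CI is below 1.8. Only if so, noninferiority will be concluded for the other comparison if the upper limit of its 2-sided 95% CI is below 1.8. The 97.5% CI will be reported for both comparisons, together with the 95% CI used for the second decision.*

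Keep the target at 442. In Power and Sample Size Calculation, one sentence can note that the calculation at 0.0125 is conservative under this rule.

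The change must be fixed and dated before outcome data are seen, since it relaxes a published primary rule in an open-label trial. It costs a few sentences and no data. The price is the one named above: a second claim may stand beside a 97.5% interval that crosses 1.8, and its error rate once the other comparison has succeeded is 0.025 instead of 0.0125.
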